**Methods/design:**

This is a randomized, placebo-controlled, double-blind study; it will be conducted in the General Hospital of Ningxia Medical University. The target study subjects are at least 18 years old, and are hospitalized cancer patients who are receiving routine opioids to control cancer-related pain but still experience breakthrough pain. A total of 240 patients will be recruited and randomly allocated between three treatment groups (A, B, C) and a control group (group D) in a ratio of 3:1. All treatment groups (A, B, C) will receive standard pain treatment (oral immediate-release morphine) plus a pre-prepared nitrous oxide/oxygen mixture, and the control group (D) will receive the standard pain treatment plus oxygen. Patients, doctors, nurses, and data collectors are all blind to the experiment. Assessments will be taken before treatment (T0), at 5 min (T1) and 15 min (T2) during treatment, and at 5 min after treatment (T3). The primary endpoint measures will be the percentage of patients whose pain is relieved at T1, T2, and T3. Secondary outcome measures will include the safety of treatment, adverse events, and satisfaction from both health professionals and patients.

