### Randomization, allocation concealment, and binding

Owing to the severity of the pain, ethicists suggest helping as many suffering patients as possible. In total, 240 participants will be randomized into four groups in a ratio of 3:1; three treatment groups (A, B, C), *n* = 180, and one control group (D), *n* = 60. The allocation sequence of each patient is decided by a computer-generated schedule, which is numbered by a statistician. The randomization schedule will be kept and sealed in an independent research room. Apart from the project manager, who is responsible for gas distribution, no other nurses or data collectors will have access to the data allocation. The nurse is blind to the double-blind randomized controlled trial lists (see Additional file 3) because the list does not indicate what treatment letters A, B, C, and D stand for.

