### Sample size determination

According to our previous study on burn-dressing pain [17, 37], we used preliminary observational data obtained in medical oncology for 20 patients. We found that 90% of patients receiving pre-prepared nitrous oxide/oxygen mixture experienced pain relief (a decrease of at least 30% in pain intensity [47]) at 15 min versus 10% of patients in the control group. The aim of this study is to assess the efficacy of the nitrous oxide/oxygen mixture, so a sample size of 12 was targeted with a two-tail test with type-1 error rate of 0.05 and a power of 90% to be sufficient. We decided on a sample size of 240 to meet the Chinese Food and Drug Administration standard for feasibility and the safety of nursing staff in implementing this analgesic [17].

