### Data management and analysis

Before the study, all data collectors will be trained in the data collection procedure. Data from withdrawn patients will not be used in the final analysis. SPSS version 22.0 (SPSS Inc., IBM Company, Chicago, IL, USA) will be used to conduct quantitative analysis following the intention-to-treat principle for a case-control randomized trial. Descriptive statistics will be analyzed by medians (inter-quartile ranges), means (standard deviations), and proportions (exact binomial 95% confidence intervals), as appropriate. Proportions will be compared by using the chi squared test or the Fisher’s exact test. Means will be compared using Student’s *t* test (normal distribution parameters) or a nonparametric two-sample Mann–Whitney test (non-normal distribution parameters). Statistical significance will be considered for *P* < 0.05.

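### Student's equal-variance t test for gas-versus-control means at 180 versus 60 loses its 5% level if the arms differ in spread; Welch's test avoids this at almost no cost (secondary means only)

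*Protocol article*

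**What the plan says.** Under Data management and analysis, the protocol article says: "Means will be compared using Student’s *t* test (normal distribution parameters"), "or a nonparametric two-sample Mann–Whitney test (non-normal distribution parameters"). The level is set in the same paragraph: "Statistical significance will be considered for *P* < 0.05". Normality is the only stated criterion for choosing between the two tests. The paragraph mentions neither equality of variances nor an unequal-variance version of the t test.

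Under Randomization, the arm sizes are given as "three treatment groups (A, B, C), *n* = 180, and one control group (D), *n* = 60". The abstract describes one treatment for all three lettered groups: "All treatment groups (A, B, C) will receive standard pain treatment (oral immediate-release morphine) plus a pre-prepared nitrous oxide/oxygen mixture". The Treatments section likewise speaks of one experimental and one control group. The natural comparison of means is therefore 180 against 60.

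The article gives no SD for any continuous measure in either arm.

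**The concern.** In its standard meaning, Student's t test estimates one SD common to both arms. With equal arm sizes a violation of that assumption does little harm. With unequal sizes it biases the standard error in a known direction:

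- **Controls more variable.** The pooled SD, dominated by the 180 gas patients, understates the uncertainty of the control mean. The test rejects too often and intervals are too narrow.
- **Gas arm more variable.** The pooled SD overstates the uncertainty. Intervals are too wide and real differences are missed.

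The switch to Mann–Whitney offers no protection, because data can be normal in each arm and still differ in spread. What is at stake is the level and interval coverage for mean differences in approximately normal secondary or descriptive measures. Heart rate and blood pressure, both recorded at every assessment, are the clearest candidates.

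**Working it through.** **Inputs from the article:** n = 180 (gas), n = 60 (control), significance at P < 0.05. The sample size section specifies a two-tailed test.

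**Assumed:** normal data, equal true means, and an SD ratio between 1 and 2 in either direction.

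**Plan's own figure.** The figure to reproduce here is the nominal 5%. With equal SDs the simulated level of the pooled test is 5.0%, so the plan's level is right in that case. The sample size of 12 concerns proportions and does not bear on this point.

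**Formulas**, with s₁ the gas SD and s₂ the control SD:

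- Pooled variance: (179·s₁² + 59·s₂²)/238
- SE² used by the test: pooled variance × (1/180 + 1/60)
- True SE²: s₁²/180 + s₂²/60
- Approximate level: P(|Z| > 1.970 × √(SE² used / true SE²)), where 1.970 is the two-sided 5% point of t on 238 df

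**Worked case, control SD twice the gas SD:**

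- Pooled variance = (179 × 1 + 59 × 4)/238 = 415/238 = 1.744
- SE² used = 1.744 × 0.02222 = 0.0388
- True SE² = 1/180 + 4/60 = 0.0722
- Ratio of standard errors = √(0.0388/0.0722) = 0.73
- Level = P(|Z| > 1.970 × 0.7325) = P(|Z| > 1.443) = 14.9%

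**All cases**, with 400,000 simulated trials for each:

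| Gas SD : control SD | SE used / true SE | Level, formula | Level, simulated | Welch, simulated |
|---|---|---|---|---|
| 1 : 1 | 1.00 | 4.9% | 5.0% | 5.0% |
| 1 : 1.25 | 0.90 | 7.8% | 7.9% | 5.0% |
| 1 : 1.5 | 0.82 | 10.5% | 10.6% | 5.0% |
| 1 : 2 | 0.73 | 14.9% | 15.2% | 5.0% |
| 1.25 : 1 | 1.12 | 2.8% | 2.9% | 5.0% |
| 1.5 : 1 | 1.22 | 1.7% | 1.7% | 5.0% |
| 2 : 1 | 1.36 | 0.7% | 0.8% | 5.0% |

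The formula uses a normal reference and the expected pooled variance, so it runs slightly below the simulation.

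**Intervals.** Coverage of the nominal 95% interval is 100% minus the level in the table, whatever the true mean difference. At a ratio of 1.5 it is about 100 − 10.6 = 89.4% if controls are more variable, and 100 − 1.7 = 98.3% if the gas arm is.

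**Power.** For a difference that Welch's test detects with 80% power, Student's test has 74%, 67% and 56% when the gas arm is more variable by factors of 1.25, 1.5 and 2 (40,000 simulated trials per setting).

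**Equal group sizes.** With 60 against 60, the pooled test stays at 5.0% to 5.3% at every ratio tried.

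**The case against.** The case against giving this much weight is strong, and most of it stands.

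- **No documented spread.** The article supplies no SDs, so every figure away from 5% depends on an assumed ratio. This stands.
- **A true null gives equal spread.** If the gas did nothing at all, randomisation would give both arms the same distribution and the level would be 5%. A reader might infer that the plan would declare an inert gas effective in up to 15% of trials; that does not follow. The inflated level applies to equal means with unequal SDs. What survives is that a gas which changes spread leaves interval width wrong, and power too when the gas arm is the more variable, whether or not the mean moves.
- **Pain scores are a poor example.** A mixture of relieved and unrelieved patients on a 0–10 scale fails a normality test in nearly every simulated trial, so the plan would send it to Mann–Whitney. At the article's own relief rates of 90% and 10%, the two spreads are equal in any case. A reader might also cite oxygen saturation compressed by the control gas, but the gas arms inhale oxygen too, and the article does not support a ceiling in one arm only. The five-point satisfaction scale is also unlikely to be normal.
- **The article may be shorthand.** It never says that variances are pooled, and a fuller document could specify Welch's test. That is possible, but the article names a test rather than leaving the choice open, and the usual meaning of that name is the equal-variance test.

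**Conclusion.** The point holds as a minor one. Under the usual reading of Student's t test, a gas-versus-control comparison of means at 180 to 60 keeps its 5% level only if the SDs are equal. At an assumed SD ratio of 1.25 to 2 the level is about 8% to 15% with more variable controls, and about 3% to 0.7% with a more variable gas arm. Interval coverage is off by the same amounts.

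The 15% should not be read as a maximum. It belongs to a twofold ratio, which the article does not support; a threefold ratio gives about 20%, and the limit is about 26%.

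The point covers only approximately normal secondary or descriptive means. The primary endpoint is a percentage and is untouched. There is no distortion if the SDs are equal, and practically none if groups A, B and C are each compared separately with D.

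**What to change.** Under Data management and analysis, replace Student's t test with Welch's unequal-variance t test for every comparison of gas and control means. Specify it in advance rather than choosing it by a Levene test, and take the 95% confidence interval for the mean difference from the same analysis. In SPSS this is the output row for equal variances not assumed, so no new software is needed.

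The cost is some degrees of freedom when the SDs are in fact equal. Welch's df is then (1/180 + 1/60)² / [(1/180)²/179 + (1/60)²/59] ≈ 101 instead of 238. The critical value moves from 1.970 to 1.984, which widens the interval by 1.984/1.970 − 1 = 0.7%.

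The change does not alter the Mann–Whitney branch, which is itself off-level as a test of equal means when spreads differ: 10.5% and 2.2% in simulation at a twofold ratio in the two directions.

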## Discussion

Many studies on transmucosal fentanyl showed excellent breakthrough pain reduction after 15 min administration [11, 23, 30, 48]. But that means patients have to suffer for at least 15 minutes severe pain. Furthermore, this fentanyl preparation is unavailable in China. In addition to the incompliance and adverse effects of oral immediate-release morphine, many other opioid formulations also appeared incapable of effectively relieving breakthrough pain due to their slow onset of actions (15–60 minutes) [11, 23, 30, 48]. This study intends to find a better alternative rescue medication for cancer patients with breakthrough pain in China.

The study of Li et al. on burns-dressing procedure pain showed faster pain reduction, within 15–20 s, for the pre-prepared nitrous oxide/oxygen mixture group [17, 37]. However, another study found that inhaled nitrous oxide showed a non-significant reduction in pain scores in metastatic dying patients with cancer-related incident pain [49]. In this study, we will attempt to verify both the analgesic efficacy of the fixed nitrous oxide/oxygen mixture, and patients’ and healthcare workers’ satisfaction in using the nitrous oxide/oxygen mixture for breakthrough pain management.

To our knowledge, this study is the first randomized controlled trial to evaluate the effectiveness of the pre-prepared nitrous oxide/oxygen mixture to treat breakthrough pain in cancer patients with advanced disease. If this treatment appears beneficial, this study can help to generate preliminary guidelines on breakthrough pain management in cancer patients with advanced disease. We intend to disseminate the results of this study to international journals and conferences.

### Trial status

Patient recruitment will start on 24 July 2016.
